# Comparative evaluation of intensified short course regimen and standard regimen for adults TB meningitis: a protocol for an open label, multi-center, parallel arms, randomized controlled superiority trial (INSHORT trial)

**DOI:** 10.1186/s13063-024-08133-6

**Published:** 2024-05-02

**Keywords:** Randomized controlled trial, Tuberculous meningitis, High-dose rifampicin, Moxifloxacin, Intensified regimen, Aspirin

## Abstract

**Background:**

Despite several incremental improvements in the management of tuberculous meningitis (TBM), the mortality rates remain high. In spite of national and international guidelines, variation in the choice, dose, and duration of drugs exist between countries and clinicians. We propose to evaluate a shorter and more effective regimen containing agents with augmented intracerebral drug exposure and anti-inflammatory approaches to improve disability-free survival among patients with TBM. Our strategy incorporates the various developments in the field of TBM over the last two decades and only few trials have evaluated a composite of these strategies in the overall outcomes of TBM.

**Methods:**

An open label, parallel arms, randomized controlled superiority trial will be conducted among 372 participants across 6 sites in India. Eligible participants will be randomly allocated in 1:1:1 ratio into one of the three arms. The intervention arm consists of 2 months of high-dose rifampicin (25 mg/kg), moxifloxacin (400 mg), pyrazinamide, isoniazid, aspirin (150 mg), and steroids followed by rifampicin, isoniazid, and pyrazinamide for 4 months. The second intervention arm includes all the drugs as per the first arm except aspirin and the patients in the control arm will receive treatment according to the National TB Elimination Program guidelines. All participants will be followed up for 1 year after the treatment.

**Discussion:**

Current WHO regimens have agents with poor central nervous system drug exposure and is too long. It does not reflect the accumulating evidence in the field. We propose a comprehensive clinical trial incorporating the emerging evidence accrued over the last two decades to shorten the duration and improve the treatment outcomes. This multi-centric trial may generate crucial evidence with policy and practice implications in the treatment of TBM.

**Trial registration:**

Clinical Trial Registry India CTRI/2023/05/053314. Registered on 31 May 2023 (https://ctri.nic.in/Clinicaltrials/pmaindet2.php?EncHid=ODYzMzg=&Enc=&userName=CTRI/2023/05/053314). ClinicalTrials.gov NCT05917340. Registered on 6 August 2023 (https://classic.clinicaltrials.gov/ct2/show/NCT05917340).

**Protocol version:**

Version 1.3 dated 12 July 2023.

**Supplementary Information:**

The online version contains supplementary material available at 10.1186/s13063-024-08133-6.

## Background

Tuberculosis (TB) is a devastating disease that leads to significant morbidity and mortality. According to the Global TB report of World Health Organization (WHO), 7.5 million individuals were newly diagnosed with TB and 1.3 million succumbed to the disease [1]. Tuberculous meningitis (TBM) is a severe form of TB with high mortality and morbidity. Even though TBM contributes to 2% of all TB cases in low HIV prevalence settings, it accounts for 20 to 69% short-term mortality with standard anti-tuberculosis therapy (ATT) [2–5]. The case fatality ratio for central nervous system (CNS) TB is about 35% among all forms of TB in India [6]. A similar proportion of patients are also severely disabled with TBM [7]. A nationwide population-based cohort study with a 30-year follow-up revealed that TBM patients in Denmark had nearly twofold increased long-term risk of mortality compared to the general population [8]. The most common complications associated with TBM include hydrocephalus, hemorrhage, arachnoiditis, and formation of tuberculoma. The most commonly reported long-term neurological sequelae are motor deficits, epilepsy, cognitive impairment, and cranial nerve palsies [9, 10]. Stroke occurs in 15–57% of patients, of whom 20% suffer long-term neurological deficits [11].

The causes of mortality and morbidity in TBM are multifactorial, complicated by delayed presentations and poor diagnostic tests. The drug therapy used for TBM in adults and children also has significant limitations. The Infectious Disease Society of America, the American Thoracic Society, and the Centers for Disease Control and Prevention advise a regimen with 2-month intensive phase consisting of isoniazid, rifampicin, pyrazinamide, and ethambutol (HRZE) followed by 7 to 10 months of rifampicin and isoniazid (HR) in the continuation phase [12]. WHO recommends a 12-month regimen with 2 months of isoniazid, rifampicin, pyrazinamide, and ethambutol followed by 10 months of isoniazid and rifampicin in adults. The recent guidelines update supports a 6-month intensive regimen containing ethionamide (6HRZEto) for children and adolescents with TBM without evidence or suspicion of drug resistant tuberculosis (DRTB) [13]. Given the scarcity of available evidence concerning the optimal selection, dosage, and duration of antituberculous treatment (ATT), multiple regimens of varying duration are also being practiced. Additionally, the number of drugs administered differ during both the intensive and continuation phases. In addition to anti-TB drugs, there is also considerable variation in practice regarding the dose and duration of adjuvant therapy with corticosteroids and aspirin.

In designing this trial, our approach is guided by two principles. We wanted the intervention to reflect the improvements made in the field recently, including high-dose rifampicin and addition of fluoroquinolones and aspirin. We propose a novel clinical trial to demonstrate the efficacy of short course therapy compared to standard of care. The drugs and doses proposed in this trial have individually been shown to be beneficial and efficacious in the treatment of pulmonary tuberculosis and TB meningitis. However, they have not been evaluated for cumulative benefit. The INTENSE TBM trial that used high-dose rifampicin and linezolid evaluated mortality alone as an outcome and considered 30% reduction in mortality [14]. We hypothesize that intensified short course (6 months) ATT with high-dose rifampicin and moxifloxacin given along with corticosteroids and aspirin will significantly reduce mortality and disability in adults with TBM compared to 12 months of standard ATT regimen. We assume our study regimen will be superior to the control regimen in terms of reducing death or disability by at least 20%.

## Methods

This study protocol has been developed following the recommendations of SPIRIT (Standard Protocol Items: Recommendations for Interventional Trials) 2013 Statement, a guideline for a clinical trial protocol [15]. The SPIRIT checklist and flow diagram of this study protocol are shown in Additional file 1.

### Objectives

Our primary objective is to demonstrate the superiority of the intensified short course (6 months) ATT regimen containing high-dose rifampicin and moxifloxacin and standard ATT regimen (12 months) in reducing composite outcome of mortality or disability among adults with TBM. Secondary objectives are to assess the safety and tolerability of high-dose rifampicin and moxifloxacin when given daily for 8 weeks and pyrazinamide administration for 6 months. We also aim to compare the pharmacokinetic (PK) parameters of ATT in the serum and cerebrospinal fluid (CSF) between the three arms, and to compare the health-related quality of life between the intervention and control arms.

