### Treatment allocation

#### Arm 1 (intensified ATT with aspirin)

Participants in this arm will receive a high dose of rifampicin 25 mg/kg once daily and moxifloxacin (400 mg once daily) along with isoniazid and pyrazinamide for 2 months. Steroids will be administered to participants with MRC grades 1 and 2 for a duration of 6 weeks, while participants in grade 3 will be treated for 8 weeks. This regimen will also be intensified with 150 mg of aspirin once daily. Intensive phase will be followed by standard doses of rifampicin, isoniazid, and pyrazinamide for the next 4 months in the continuation phase (Fig. 1).

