#### Arm 2 (intensified ATT without aspirin)

Participants in this arm will receive intensified ATT regimen and steroids like arm 1 but without aspirin in the intensive phase and standard doses of isoniazid, rifampicin, and pyrazinamide for the next 4 months in the continuation phase.

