#### Arm 3 (control arm)

The control arm will receive treatment according to the standard national guidelines for TBM. They will receive a first-line regimen consisting of 2 months of isoniazid, rifampicin, ethambutol, and pyrazinamide followed by 10 months of isoniazid, rifampicin, and ethambutol daily in a fixed-dose combination (FDC) as per the various weight bands in National TB Elimination Programme of India. Participants will also receive steroids as in the other two arms.

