### Sample size

The trial is powered to assess the superiority of intensified regimen (arm 1) compared to control regimen (arm 3). A systematic review and meta-analysis on treatment outcomes in TBM done by Stadelman et al. reported the proportion of mortality and disability after treatment is 24% and 32%, respectively [7]. The proportion of composite outcome (death or disability) is 56%. We assume a 20% reduction of composite outcome with our intervention (i.e., from 56 to 36%). We used the formula for Z test for comparing proportion between two groups (arm 1 and arm 3). Hence, to study the impact of “Intervention” compared to “Standard care” in reducing the composite outcome (death or disability), expecting a minimum difference of 20% between intervention arm with aspirin (arm 1) and control arm (arm 3), assuming 85% power of the study, 5% level of significance, 2-sided significance test; the required sample size was 112 patients in each arm. Considering 10% lost to follow-up, the total sample size was calculated as 372 with 124 in each arm. Previous clinical trials in TBM have evaluated mortality as an outcome and considered 30% reduction [14]. Since we propose to evaluate composite outcome of death or disability, we have assumed a conservative effect size of 20% reduction. The 10% loss to follow-up is assumed based on the previous TBM trials as well as randomized controlled trials conducted at ICMR-NIRT, Chennai [20, 21].

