While the mortality due to TBM among hospitalized patients was 42%, disability among them has been reported as 32% leading to poor quality of life among survivors [7, 35]. This highlights the importance of measuring disability as a primary outcome in addition to mortality. Evidence suggests that aspirin reduces the new-onset stroke, a major cause of disability in patients with TBM by significantly reducing perivascular inflammation. According to a meta-analysis with 365 participants from three randomized trials, aspirin effectively decreased the incidence of new-onset stroke with a number needed to treat of 10 [36]. The doses of aspirin used in these trials also varied widely. A trial from India showed lower dose aspirin (150 mg/day) when used along with steroids prevented new infarcts and reduced strokes and mortality [37]. In contrast, Schoeman et al. demonstrated in an open-label trial that aspirin use, regardless of dosage, did not significantly reduce mortality and morbidity (hemiparesis) [38]. Hence, it is vital to prove the efficacy of aspirin in reducing the stroke with an adequate dose for an appropriate period. Thus, we propose 150 mg of aspirin to all TBM patients in one of the intervention arms for 2 months. Thwaites et al. showed in a large RCT, that while there is a significant reduction in mortality in the steroid group, the proportion of patients with severe disability was higher (18.2 vs 13.2%) [39]. An almost-quarter reduction in mortality was observed with the use of steroids, according to a systematic review and meta-analysis comprising 9 trials involving 1337 participants (RR-0.75, 95% CI: 0.65–0.87). Additionally, the analysis concluded that steroid use might have minimal or no impact on the neurological deficit [40]. The role of adjunctive strategies like aspirin on disability needs further study.

In conclusion, the mortality and morbidity with the currently used regimens are very high despite current treatment regimens. Studies evaluating shorter, more efficacious regimens are urgently needed. We optimize currently available common drugs in this RCT to impact morbidity-free survival in tuberculous meningitis.

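### The primary objective concerns the anti-TB regimen alone, but the only powered comparison (arm 1 vs arm 3) also differs in aspirin, so a positive result supports the package and not the regimen by itself

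*Protocol article*

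**What the plan says.** The Objectives section of the protocol article sets out to "demonstrate the superiority of the intensified short course (6 months) ATT regimen containing high-dose rifampicin and moxifloxacin", set against the 12-month standard regimen. Aspirin appears in neither the primary nor the secondary objectives.

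The Sample size section ties the calculation to one pair of arms: "The trial is powered to assess the superiority of intensified regimen (arm 1) compared to control regimen (arm 3". It then identifies arm 1 as the aspirin arm: "expecting a minimum difference of 20% between intervention arm with aspirin (arm 1) and control arm (arm 3".

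The treatment sections define the arms:
- Arm 1, after the intensified ATT and steroids: "This regimen will also be intensified with 150 mg of aspirin once daily".
- Arm 2: "Participants in this arm will receive intensified ATT regimen and steroids like arm 1 but without aspirin in the intensive phase".
- Arm 3: "They will receive a first-line regimen consisting of 2 months of isoniazid, rifampicin, ethambutol, and pyrazinamide followed by 10 months" of continuation treatment. Steroids are given as in the other arms and no aspirin is listed.

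The Background hypothesis differs from the objective. It puts aspirin and corticosteroids together with the intensified ATT as the intervention expected to reduce death and disability.

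The Data analysis section describes a log-rank comparison across the three arms and a two-sided 5% criterion for superiority between two groups. It does not say which two.

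**The concern.** The objective asks about one change, the ATT regimen. The powered comparison makes two changes, the ATT regimen and aspirin. The document also gives reasons to think the second change could act on the primary outcome. The Discussion describes stroke as a leading cause of disability in this disease and reports from a meta-analysis that "aspirin effectively decreased the incidence of new-onset stroke with a number needed to treat of 10". Disability is half of the primary composite.

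What is at stake is what the trial may claim. If arm 1 does better than arm 3, a reader who takes the objective at its word could credit the six-month ATT regimen with a benefit to which aspirin contributed an unknown part. The arm that separates the two effects is already in the design, but the article does not link it to the objective.

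**Working it through.** **Step 1. What differs between the arms**

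| Contrast | ATT differs | Aspirin differs | Steroids differ | Question answered |
|---|---|---|---|---|
| Arm 1 vs arm 3 | yes | yes | no | the package |
| Arm 2 vs arm 3 | yes | no | no | the ATT regimen |
| Arm 1 vs arm 2 | no | yes | no | aspirin added to intensified ATT |

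The objective's wording matches the second row. The Background hypothesis and the Sample size section match the first.

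**Step 2. Reproduce the stated sample size**

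Inputs from the Sample size section: 56% vs 36%, two-sided 5%, 85% power. Pooled z-test for two proportions:

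n = [1.960·√(2·p̄·q̄) + 1.036·√(p₁q₁ + p₂q₂)]² / d²

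With p̄ = 0.46 and d = 0.20:
- √(2 × 0.46 × 0.54) = √0.4968 = 0.705
- √(0.2464 + 0.2304) = √0.4768 = 0.691
- n = (1.381 + 0.716)² / 0.04 ≈ 110 per arm, against 112 stated

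Power at 112 per arm is Φ[(0.20·√112 − 1.381) / 0.691] = Φ(1.06) = 85.6%. For loss to follow-up, 112 × 1.10 ≈ 124 per arm, and 3 × 124 = 372. The stated figures reproduce, so the arithmetic is not in question.

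**Step 3. Power for the contrast that isolates ATT**

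The 20-point effect is set for ATT plus aspirin. The document gives no effect for ATT without aspirin, so the ATT effects below are assumptions. The same formula is used, with 112 evaluable per arm, a 56% control rate and two-sided 5%.

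| Assumed ATT effect (arm 2 vs arm 3) | Left for aspirin out of 20 points | Power |
|---|---|---|
| 20 points (56% vs 36%) | 0 | 85.6% |
| 18 points (56% vs 38%) | 2 | 77% |
| 15 points (56% vs 41%) | 5 | 61% |
| 10 points (56% vs 46%) | 10 | 32% |

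The spread is illustrative. A number needed to treat of 10 means about 10 strokes prevented per 100 patients.
- If only 20% of those would have left a lasting deficit (the Background's figure for stroke patients), aspirin accounts for 10 × 0.20 = 2 points, leaving 18 for ATT.
- If every one would have led to death or disability, it accounts for 10 points, leaving 10.
- 15 points is an intermediate value.
- 20 points corresponds to no aspirin effect.

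The table treats the two effects as additive. It uses proportions because that is how the trial was sized, although the analysis is planned as time to event.

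**The case against.** The strongest reply is that the package is plainly what the investigators intend. The abstract speaks of combining better brain drug exposure with anti-inflammatory treatment, the hypothesis includes aspirin, and the Sample size section labels arm 1 as the aspirin arm. On this view the Objectives section is the outlier and the defect is one sentence. That stands as a description of intent, and it points to the repair. The stated objective still names a different intervention from the one being tested.

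Three further points limit the concern:

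- Arm 2 is randomised at the same size as the other arms, so evidence on ATT alone will be collected. If aspirin adds nothing, arm 2 vs arm 3 has the same power as the primary contrast. The Discussion makes that possible: it cites a trial in which aspirin at any dose gave no significant reduction in mortality or hemiparesis, notes that doses varied widely across trials, and calls for further study of aspirin's role in disability.
- The Sample size section already confines its 85% power to arm 1 vs arm 3. The document does not claim that power for other contrasts.
- The statistical analysis plan is not shown and may specify the pairwise contrasts. Their absence from the article is not the point here. No analysis plan can turn arm 1 vs arm 3 into evidence for ATT alone.

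A reader might also infer that the plan commits itself to declaring the ATT regimen superior once arm 1 beats arm 3. It does not: no section gives such a decision rule, and the Objectives section names no arms. Nor do the documents support saying that aspirin could explain the whole difference. The conversion in the working gives it 2 to 10 of the 20 points, and that conversion from strokes to the composite is an assumption the document never makes.

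**Conclusion.** The concern holds as a mismatch between stated texts. The objective is about ATT. The powered contrast and the hypothesis are about ATT plus aspirin. A positive arm 1 vs arm 3 result supports the package and cannot by itself support the claim in the Objectives section. That claim needs arm 2 vs arm 3.

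This conclusion rests on the arm definitions alone and needs no assumption about how well aspirin works. Its size does need one: power for the ATT-only contrast runs from about 86% to 32% as the assumed ATT effect falls from 20 to 10 points. The 32% figure should not be read as the expected case, since it requires every prevented stroke to avert a death or disability. Using the document's own 20% figure for lasting deficit gives 77%.

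The point should be corrected because it governs what the trial may conclude. It does not threaten the arms, the sample size or the test of the Background hypothesis.

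**What to change.** 1. Restate the primary objective as superiority of intensified short-course ATT with aspirin (arm 1) over standard treatment (arm 3), in line with the Background hypothesis and the Sample size section.
2. State that a positive arm 1 vs arm 3 result supports the package only.
3. Base any claim about the ATT regimen itself on arm 2 vs arm 3, reported with a confidence interval.

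The cost is wording and a narrower headline claim. Arms, sample size and data collection do not change. The Trial status section says recruitment had not begun at the time of writing, so the objective could be settled at that stage without knowledge of any outcome.

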### Study design and setting

This is an open label, multi-center, parallel arms, randomized controlled superiority trial. The trial will be conducted across six sites located in different geographical regions in India. These sites are tertiary referral centers and well equipped with advanced laboratories, imaging facilities, and expertise to manage TBM and its complications. ICMR-National Institute for Research in Tuberculosis (ICMR-NIRT) will function as a primary sponsor and nodal coordinating center for the trial.

### Study population and eligibility criteria

Participants for the trial will be identified based on the Lancet consensus scoring system for the diagnosis of TBM [16]. This scoring system has 20 parameters divided into 4 categories: clinical, CSF, CNS imaging, and evidence of TB elsewhere. The maximum score is 20. If there is evidence of acid fast bacilli (AFB) in CSF smear, culture, or TB in histopathology of the brain or spinal cord, it is termed as a definite diagnosis of TBM. When the total score is > 10 with no CNS imaging, or > 12 with imaging, it is considered as probable diagnosis. A possible diagnosis is made with scores between 6 and 9 without imaging or 6–11 with imaging. All adults (> 18 years) with either definite, probable, or possible TBM as per the criteria will be eligible for the study. These participants should also be willing to undergo HIV test, consent, and adhere to trial procedures and follow-up schedule. They should also be residing within 100 km of the study sites. The female participants in the reproductive age group should agree to use effective barrier contraception during the period of the treatment.

We will exclude the patients if they have any of the following criteria: (1) known current/previous drug resistance to ATT such as rifampicin, isoniazid and luroquinolones; (2) concurrent or known diagnosis of any other meningitis such as bacterial, viral, and fungal; (3) currently having an uncontrolled cardiac arrhythmia or ECG abnormalities which are contradiction for the administration of moxifloxacin including prolonged QTc which is defined as > 450 ms in males and > 460 ms in females measured in lead II or V5 on a standard 12-lead ECG [17]; (4) has clinical icterus or hepatic impairment characterized by serum bilirubin level above the normal laboratory reference range with abnormal liver enzymes, or isolated alanine aminotransferase and/ or aspartate aminotransferase levels above five times the upper limit of the normal laboratory reference range [18]; (5) previous history of ATT, if any, should not exceed 1 month in the past and not more than 7 days in the preceding 1 month; (6) pregnant or lactating women; (7) rapid clinical deterioration or very sick and moribund during the screening process, renal failure, liver disease, or any condition (social or medical) that in the opinion of the investigator would make trial participation unreliable or unsafe; and (8) has a known allergy to any of the drugs proposed to be used in the trial regimen.

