### Randomization

Computer generated list of random numbers using permuted block randomization will be created and uploaded in RedCap data base.When all the screening results are available and within the normal range, the patient will be randomly allocated in a ratio of 1:1:1 to one of the treatment groups. The study sites will be required to ensure inclusion and exclusion criteria for each patient prior to enrolment and enter the data in the baseline case report form with the eligibility criteria in RedCap data base. Upon verification of the case report form and the eligibility criteria, the ICMR-NIRT statisticians (randomization team) will approve for randomization and site investigators can proceed for online randomization in Redcap.

 Allocation concealment will be ensured, as the randomization team will not approve the randomization until the patient has been recruited into the trial, which takes place after all baseline assessments are completed. The intervention will be administered by the site investigators who will also be treating physicians.

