### Participant timelines and follow-up

In this assessment, demographic details, medical history, clinical examination, neurological assessment including Modified Rankin Score (MRS) and Glasgow Coma Scale (GCS), sociological assessment for compliance to trial procedures, and all other study procedures will be done. Blood will be collected for hematological (complete blood count—CBC) and biochemical tests (sugar, HbA1C, liver, and renal function tests), HBsAg, and HIV. Patients will also undergo CT or MRI imaging of the brain. We will also collect sputum for CBNAAT and AFB culture and do chest X-ray to rule out pulmonary TB. All eligible patients will be enrolled into the trial. At the time of enrolment, blood will be collected for immunological biomarkers (CRP, TNF-α, monocyte and dendritic cell functions, and other cytokines).

During the study period, patients will be followed as per the study schedule attached (Table 1). After admission to the study and treatment allocation, participants will be followed up every week for the first 2 months and monthly till the completion of the treatment. They will undergo clinical examination including detailed neurological examination and adverse event (AE) monitoring. After treatment completion, all participants will be followed up once in 3 months for a period of 12 months. Participants in the study arms I and II will complete 12 months of post-treatment follow-up at the 18th month study visit and participants in the control arm will complete their post-treatment follow-up at the 24th month study visit.

**Table 1 Tab1:** Study schedule

S No	Investigations	Pre-screening	Screening	Enrolment	W1	W2	W3	W4	W5	W6	W7	W8	M3	M4	M5	M6	M7	M8	M9	M10	M11	M12	M15	M^a^18	M21	M24
1	Screening consent		✓																							
2	Assess eligibility		✓	✓																						
3	Informed consent			✓																						
4	History and clinical examination		✓	✓	✓	✓	✓	✓	✓	✓	✓	✓	✓	✓	✓	✓	✓	✓	✓	✓	✓	✓	✓	✓	✓	✓
5	GCS		✓	✓	✓	✓	✓	✓	✓	✓	✓	✓	✓	✓	✓	✓			✓			✓	✓	✓	✓	✓
6	Modified Rankin’s score		✓	✓	✓			✓				✓		✓		✓			✓			✓	✓	✓	✓	✓
7	Sputum smear and MGIT^b^		✓																			✓		✓		
8	CSF analysis for AFB smear, MGIT, Xpert, and to rule out other etiology as appropriate	✓																								
19	CSF cytology, biochemistry,	✓																								
10	HIV		✓																							
11	Urine pregnancy test^c^		✓					✓				✓	✓	✓	✓	✓	✓	✓	✓	✓	✓	✓				
12	Hepatitis B and C		✓																							
13	LFT		✓			✓		✓		✓		✓		✓		✓			✓			✓				

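### Diagnostic scores of exactly 10 (no imaging) or 12 (imaging) fall in no eligibility class, and the normal-results condition for randomisation conflicts with the eligibility criteria

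*Protocol article*

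**What the plan says.** **Score bands** (Protocol article, Study population and eligibility criteria). The score has a maximum of 20. Three classes are defined:

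- Definite, by laboratory or tissue evidence whatever the score: "If there is evidence of acid fast bacilli (AFB) in CSF smear, culture, or TB in histopathology of the brain or spinal cord".
- Probable: "When the total score is > 10 with no CNS imaging, or > 12 with imaging, it is considered as probable diagnosis".
- Possible: "A possible diagnosis is made with scores between 6 and 9 without imaging or 6–11 with imaging".

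Adults "with either definite, probable, or possible TBM as per the criteria will be eligible for the study". On imaging, Participant timelines and follow-up states: "Patients will also undergo CT or MRI imaging of the brain". Table 1 places CT/MRI at the screening visit.

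**Condition for randomisation** (Randomization). "When all the screening results are available and within the normal range, the patient will be randomly allocated". The same section then has sites check the inclusion and exclusion criteria, and has the central statisticians approve randomisation once the form and the criteria have been verified.

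**Provisions that bear on that condition.** The eligibility section excludes "isolated alanine aminotransferase and/ or aspartate aminotransferase levels above five times the upper limit of the normal laboratory reference range". Table 1 schedules CD4 counts for HIV-positive participants and HbA1C for diabetics, at screening and during follow-up. Data analysis stratifies the primary outcome by HIV status and plans a sensitivity analysis confined to definite and probable cases.

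**The concern.** The possible band stops one point short of the probable cut-off, and the probable cut-off is a strict inequality. The boundary score therefore belongs to neither class. Entry requires one of the three classes, so a patient at the boundary is shut out while a patient with a lower score, and weaker evidence of TBM, is admitted. That cannot be what was intended.

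The same cut-off decides who enters the sensitivity analysis. In an open-label trial that set should be fixed before allocations are known, not settled afterwards by a judgement about boundary cases.

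The second problem is that one randomisation step carries two different conditions: normal screening results, and satisfaction of the eligibility criteria. Six sites and a central approval team need a single rule. Where they apply different ones, the result is inconsistent enrolment or avoidable eligibility deviations.

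**Working it through.** **1. The plan's own figure, for completeness.** Inputs from Sample size: 56% against 36%, two-sided 5%, power 85%.

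n = [1.960 × √(2 × 0.46 × 0.54) + 1.036 × √(0.56 × 0.44 + 0.36 × 0.64)]² / 0.20² = 110 per arm.

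The article states 112, at which power is 85.6%. Then 112 × 1.1 = 123.2, rounded up to 124, and 3 × 124 = 372. The stated figure reproduces closely enough. None of its inputs involves the score bands or the randomisation condition, so it does not move.

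**2. Classify every whole-number score from 6 to 20** for a patient without the definite criteria.

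| | Possible | Probable | In no class |
|---|---|---|---|
| No imaging | 6 to 9 | 11 to 20 | 10 |
| With imaging | 6 to 11 | 13 to 20 | 12 |

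Exactly one score per row is unassigned. Since CT or MRI is done for everyone at screening, the second row normally applies.

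**3. Repeat with contiguous bands.** With probable at ≥ 10 and ≥ 12, no score from 6 to 20 is left over. Extending possible to 6–10 and 6–12 also leaves none. Arithmetic shows that the gap must be closed, but not on which side.

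**4. Trace the consequence.** A non-definite patient scoring 12 with imaging is either turned away (an eligibility effect) or enrolled (a classification effect in the sensitivity analysis). Only one of these can happen to a given patient, but the text leads to one or the other.

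**5. Set the normal-results condition beside the rest of the article.**

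| Screening item | Under the normal-results condition | Elsewhere in the article |
|---|---|---|
| Isolated ALT/AST between 1 and 5 times the upper limit | Not randomised | Not excluded by the liver criterion |
| HIV test | A positive result would bar entry, read literally | CD4 follow-up scheduled; primary analysis stratified by HIV status |
| Sugar or HbA1C in a diabetic | A raised value would bar entry | HbA1C scheduled for diabetics to month 12 |
| Brain CT/MRI | An abnormal scan would bar entry | CNS imaging is one of the four scoring categories |
| Gate applied by the central team | Results normal | Eligibility criteria verified |

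Every row is a conflict if the sentence is taken at its word.

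**The case against.** The strongest reply is that both are slips of wording in a journal article that condenses a fuller protocol. The score comes from a published, cited system, summarised here in two sentences, and the full protocol and the REDCap form are not shown. Sites may never meet the gap. The normal-results sentence is probably loose phrasing: the text after it makes verified eligibility the basis for approval, and a literal all-normal rule would be unworkable in a trial whose diagnosis rests partly on abnormal imaging.

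Much of this stands. It limits the harm that can be claimed, and it makes the eligibility check the likely intended gate. It does not remove the defects. Both concern what the article states, not what it leaves out, and the second still leaves two conditions on one step.

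Four stronger readings are tempting, and the document does not support them:

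- *That a known number of patients is lost.* A reader might assume a share at the boundary score and multiply it by 372. The article gives no score distribution. Patients turned away would also come from the candidate pool (80–120 per institute per year, so 6 × 80 = 480 to 6 × 120 = 720 across six sites), not from the 372 enrolled.
- *That the trial would enrol milder patients than the 56% planning rate implies.* This presumes that sites apply the sentence literally, which nothing shows.
- *That anyone with ALT/AST up to five times the upper limit is admissible.* Only isolated elevations are. Raised bilirubin with abnormal enzymes is excluded, as is liver disease.
- *That boundary scores must be probable.* The document does not say so.

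**Conclusion.** The point holds as two specific wording defects in rules the trial relies on. As printed, a non-definite patient scoring exactly 10 without imaging or 12 with imaging has no class, is ineligible, and if enrolled has no defined place in the definite-and-probable sensitivity analysis. The normal-results condition contradicts the liver-enzyme criterion, the planned inclusion of HIV-positive patients and diabetics, and the eligibility check in its own section.

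The size is one unassigned score per row, with 12 the operative one. The number of patients affected cannot be computed. Power, sample size and the method of the primary analysis are untouched. Definite cases are eligible at any score and lie outside the gap.

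The conclusion assumes that scores are whole numbers and that the printed text is what sites follow. It should be corrected, but it does not undermine the design.

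**What to change.** 1. Make the score bands contiguous. The sponsor should confirm against its cited scoring system which class takes 10 and 12. Writing ≥ in place of > for probable is one way, and it leaves the possible bands as they are.
2. In the Randomization section, replace the normal-results condition with a statement that all screening results are available and that the patient satisfies every inclusion criterion and meets no exclusion criterion. This matches the check the section already describes.
3. Carry both changes into the REDCap eligibility form, and record the diagnostic class there before randomisation, so that the sensitivity-analysis set is fixed without knowledge of allocation.

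The cost is two wording corrections and a form check, with no change to sample size or budget. The article's Trial status section reports that recruitment had not begun. Once patients are enrolled, the same ambiguity would have to be handled as eligibility deviations and disputed class assignments.
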